### Data collection and management

Data will be de-identified using a participant identification number that is coded independent of group assignment. All data are collected and analyzed without knowledge of the group assignment. Only the principal investigator and research staff will have access to the data. Demographic and clinical data from participants’ electronic medical records will be automatically extracted and entered into a Research Electronic Data Capture (REDCap) database (http://redcap.stanford.edu) that is supported by the Stanford Medicine Research IT team. Parent questionnaires will be completed with paper or electronic REDCap forms whenever possible. The REDCap platform services at Stanford are subsidized by (a) Stanford School of Medicine Research Office and (b) the National Center for Research Resources and the National Center for Advancing Translational Sciences, National Institutes of Health. For neuroimaging data, we transitioned processing to Flywheel (https://flywheel.io/), an integrated imaging processing system that uses cloud-based computing to automate analysis pipelines and allows data archiving and sharing of de-identified data.

### Harms

We do not anticipate adverse events related to exposure to maternal voice recordings. Clinical staff in the nursery already responsible for monitoring the health status of the infants will do so for the entire duration of the intervention period. In the unexpected event that an infant does not tolerate the voice recordings, the intervention will be ended immediately. There is some risk for abnormal findings on MRI scans at 12 months AA. In the event of an abnormal scan, participants will be referred to the Department of Radiology at LPCH (or other institution) for interpretation. The principal investigator assumes responsibility for contacting families about unanticipated abnormal results and will recommend families seek further consultation for their primary care physician when necessary and/or recommended by the consulting radiologist. Any unexpected adverse events will be reported to the Data Safety Monitoring Board and to the Institutional Review Board.

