## Background

Each year, approximately 400,000 infants in the United StatesUSA and 15 million worldwide are born preterm (before 37 weeks of gestation) [1]. Up to 50% of infants born less than 32 weeks of gestation develop disadvantaged outcomes, including language and related learning difficulties [2–7]. Poor language skills can lead to poor social relationships [8], academic and occupational underachievement [9], and high utilization of special education [6]. Although many studies of premature birth describe poor language outcomes [2, 6, 7, 10, 11], relatively few propose interventions beyond medical treatment [12].

Poor language outcomes in preterm children have been attributed in part to the minimal amount of maternal speech that neonates experience while hospitalized in the neonatal intensive care unit (NICU) [12–14]. Under typical developmental circumstances, maternal speech is one of the most salient acoustic stimuli experienced by a fetus [15, 16]. The sound environment of an open-bay NICU has been estimated to contain only 2–5% (~ 50 min/day) of adult speech sounds [17]. Studies in older, typically developing infants have demonstrated that the quantity and quality of language input a child experiences are tightly linked to later language skills [18, 19]. Maternal speech input during the first postnatal year is also shown to assist infants’ abilities to recognize speech sounds [20–22]. One observational study of preterm newborns found that variations in the amount of adult speech a newborn heard on a single day in the NICU at 32 and 36 weeks postmenstrual age (PMA) were positively associated with language skills at 7 and 18 months [17]. Small interventional studies have found that experimentally increasing preterm infants’ exposure to maternal speech can significantly improve short-term health outcomes [14], including improvements in oxygen saturation [23, 24], decreases in apnea and bradycardia events [25, 26], improvements in weight gain [26], feeding tolerance [27, 28], and auditory cortex thickness as measured by cranial ultrasound [29]. It is not known yet, however, whether there are sustained long-term benefits of early maternal speech exposure on language outcomes.

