#### Randomization and RCT design elements

Eligible participants will be randomized by the principal investigator ([name]), who will not be blinded, in order to provide close monitoring of the procedures. The principal investigator will allocate participants sequentially as they are enrolled to either the T or the C group using the minimization algorithm by Pocock and Simon [41] implemented in the R statistical software package [42]. Randomization will be stratified for (1) GA (24-0/7 to 27-6/7 weeks or 28-0/7 to 31-6/7 weeks), to control for potential development differences in response to the intervention and as a proxy for neural injury, and (2) socioeconomic status (SES) (above versus below average SES; based on Hollingshead Index (HI) [36, 43]), to control for potential differences in language outcomes affected by socioeconomic factors. Taking into account ethical considerations and parental preferences, twins and multiples will be assigned to the same group [44]. Families and research and clinical staff will be blinded to the group status. In the unlikely event that a family, research staff, or clinical staff suspect that an infant may not tolerate the speech recording, the principal investigator will reveal the group assignment.

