#### Analytic strategy

We anticipate that stratification prior to randomization will result in a close matching of T and C groups on demographic and health variables. Prior to statistical analyses, we will use independent samples t-tests (continuous variables) or chi-square tests (categorical variables) to assess the statistical balance between T and C groups on the basis of GA, sex, SES, clinical complications associated with premature birth, and language exposure during treatment and after hospital discharge. Analyses will use an intention-to-treat strategy [57]. If groups are matched on all variables, we will use independent t-tests (two-tailed) to compare T versus C groups on the primary long-term language outcome and the secondary short-term outcomes that relate to white matter development. Should groups not be balanced, and to account for missing data, we will use linear mixed models: T group as a fixed factor and unmatched or missing variables are random factors. Statistical significance is set at *p* < 0.05. Should an imbalance of twins or multiples occurs, we will perform group analyses including all singletons and one randomly selected twin or multiple from each set [58].

We will perform post hoc univariate and/or non-parametric analyses to determine if neural and clinical outcomes are associated with variations in the dose (i.e., number of hours of maternal speech delivered) or length (i.e., number of nights of delivery) of treatment, controlling for GA and PMA. Post hoc covariance analyses will permit further interpretation of either significant or non-significant treatment effects for short- and long-term neural and language outcomes. We will use multiple regression analyses to predict language outcomes from short-term neural and clinical outcomes, while controlling for group status and measures of language exposure.

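### Only undefined unexpected adverse events are stated to reach the safety board, and by-arm differences in clinical complications are handled as imbalance rather than reviewed as possible harm

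*Protocol article*

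**What the plan says.** **Harms.** The section starts from the expectation "We do not anticipate adverse events related to exposure to maternal voice recordings". Surveillance is by usual care: "Clinical staff in the nursery already responsible for monitoring the health status of the infants will do so for the entire duration of the intervention". For an individual infant, "In the unexpected event that an infant does not tolerate the voice recordings, the intervention will be ended immediately". The reporting rule is "Any unexpected adverse events will be reported to the Data Safety Monitoring Board and to the Institutional Review Board". Neither *unexpected* nor intolerance is defined.

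**Randomization and RCT design elements.** Families, research staff and clinical staff are blinded; the principal investigator is not. If any of the blinded parties "suspect that an infant may not tolerate the speech recording, the principal investigator will reveal the group assignment".

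**Ethics.** A committee of two neonatologists and a pediatric neuroradiologist oversees the intervention. The article does not describe what data it receives.

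**Analytic strategy.** Before the outcome analyses, t-tests or chi-square tests compare the arms on gestational age, sex, socioeconomic status, complications of prematurity, and language exposure during treatment and after discharge. If the arms differ, the unmatched variables enter a mixed model. The outcome tests between arms cover language and the "secondary short-term outcomes that relate to white matter development". A post hoc analysis relates undefined clinical outcomes to dose and length of treatment.

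**Background.** Earlier small studies of maternal speech are cited for better oxygen saturation, "decreases in apnea and bradycardia events", weight gain and feeding tolerance.

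**Data collection and management.** Demographic and clinical data from medical records "will be automatically extracted and entered into a Research Electronic Data Capture (REDCap) database".

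**The concern.** The reporting rule filters on whether a single event is unexpected. In infants born before 32 weeks, events such as apnea, bradycardia, desaturation and feeding problems can reasonably be taken as part of the ordinary course. That is a clinical assumption; the article does not say it. If it holds, a clinician judging one event at a time would often call it expected, and it would not be forwarded. A harm that takes the form of more of a common event shows up only when rates are set side by side by arm, and no such review is stated.

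The one by-arm look at complications serves another purpose. A difference there triggers model adjustment. If the complication arose after randomization and the recordings contributed to it, the plan would treat an effect of treatment as a nuisance variable. That hides the signal and may also distort the adjusted treatment effect on language or white matter.

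At stake is what the trial can say about harms after up to 9 weeks of nightly playback, when the abstract hopes the results will help guide neonatal unit practice.

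**Working it through.** **1. The plan's own figures.** The article's only sample-size figures concern language and diffusion outcomes. With a two-sample t-test at two-sided 0.05, d = 1.0 needs 16.7, so 17 per group (power 0.807). With 21 per group, power is 0.885 at d = 1.0 (stated 0.88) and 0.812 at d = 0.9 (stated above 0.8). These reproduce. None concerns harms.

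**2. Which stated element compares rates between arms?**

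| Element | Section | Compares event rates by arm as possible harm? |
|---|---|---|
| Bedside monitoring | Harms | No; infant by infant |
| Ending for intolerance | Harms | No; infant by infant |
| Revealing the group on suspicion | Randomization | No; no count by arm is stated |
| Reports of unexpected events | Harms | No; single events |
| Committee oversight | Ethics | Not stated |
| Test of complications | Analytic strategy | Compared by arm, but as balance |
| Outcome tests | Analytic strategy | Language and white matter only |
| Dose and length analysis | Analytic strategy | Not an arm comparison |

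**3. Is the balance check confined to baseline?** No cut-off is given. The list includes language exposure during treatment and after discharge, which can only arise after randomization, so the check is not baseline-only. Control variables and covariates lists infection, days of intubation and oxygen, and radiographic lung changes, all of which can accrue after randomization. Apnea, bradycardia, desaturation and feeding tolerance are not listed.

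**4. What intolerance reports from one arm could show.** With zero reports in 21 treated infants, the upper 95% limit for the true proportion is 1 − 0.05^(1/21) = 0.133 one-sided, or 1 − 0.025^(1/21) = 0.161 two-sided. This bounds intolerance reports in one arm only. It says nothing about rates of common events.

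**5. What a by-arm table could show at 21 per arm.** The article gives no event rates, so these are assumed. Two-sided 0.05; normal approximation with pooled variance under the null, and exact Fisher power by enumeration:

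| Control vs treated | Normal | Fisher |
|---|---|---|
| 20% vs 40% | 0.29 | 0.19 |
| 30% vs 50% | 0.26 | 0.16 |
| 40% vs 60% | 0.25 | 0.15 |
| 50% vs 70% | 0.26 | 0.16 |
| 30% vs 60% | 0.50 | 0.36 |
| 30% vs 70% | 0.76 | 0.63 |

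For 80% power (normal approximation), the treated rate would have to reach about 48%, 61%, 72% or 89% from control rates of 10%, 20%, 30% or 50%. For a continuous count, 80% power needs d of about 0.89; power at d = 0.5 is 0.35.

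Interval width for an observed 30% vs 50%: standard error = √(0.30×0.70/21 + 0.50×0.50/21) = √(0.0100 + 0.0119) = 0.148. The half-width is 1.96 × 0.148 = 0.29, so the 95% interval for the difference runs from about −9 to +49 points.

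**The case against.** The strongest reply is that this is a condensed article. Event definitions, committee tables and report formats usually sit in a full protocol or charter, and their absence here is no fault. That stands, and the point does not rest on it. It rests on two things the article does state: a filter for what is reported, and a balance test with no time limit that feeds covariate selection.

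Three stronger readings are tempting, and the documents do not support them.

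- *Clinical events are never compared by arm.* They are: Analytic strategy tests complications of prematurity between groups. The problem is the use made of the result.
- *Intolerance has no comparator because controls hear nothing.* Both arms have the same device and the staff are blinded, so suspicion can arise in either arm. A control count is available; the article simply does not say it will be kept.
- *Worsening cannot be detected, or the board never sees rates by arm.* Monitoring, ending for intolerance, unblinding and a committee all exist, and the article does not say what the committee reviews. The supportable statement is that no by-arm review is stated.

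Other points against also carry weight. The Background cites the common events only as improving with maternal speech, and nothing in the article says intolerance would appear through them. Infants enter when medically stable, so many complications will predate randomization. The article promises no claim of safety. At 21 per arm, a table will not reliably show moderate worsening. These limit the size of the point. They do not make it right to enter a post-randomization complication as an imbalance.

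**Conclusion.** The point holds in a limited form and is worth correcting. Under the stated rule, only events judged unexpected go to the board, and a difference between arms in complications would lead to adjustment, not to review as possible harm. The existing safeguards work at the level of the single infant; none is stated to compare rates between arms.

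Two assumptions support this: that events such as apnea and bradycardia would often be classed as expected in this population, and that at least some of the tested complications are recorded after randomization. The article's wording allows the second but does not state it.

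The gain from a correction is modest. Power for a 20-point rise is about 0.15 to 0.29 under the assumed rates, so a by-arm table describes the data and can neither reliably detect nor exclude moderate worsening. It would still give the board, and later the reader, an estimate with an interval where none is now planned.

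**What to change.** **In Harms.** Keep expedited reporting of unexpected events. Add a periodic descriptive table for the board by masked arm (A/B), covering every infant from first to last device night:

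- charted apnea, bradycardia and desaturation events;
- feeding intolerance;
- weight gain;
- transfers back to intensive care;
- suspected intolerance and early ends of the intervention, counted in both arms whatever group is then revealed.

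Take these from the electronic-record extract where it can supply them. Event counts are best shown per device-night, since the planned duration ranges from 2 to 9 weeks (14 to 63 nights). Repeat the table at the end of the trial with estimates and intervals, without significance tests. No rule for ending the intervention is proposed here.

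**In Analytic strategy.** Restrict the balance check to variables fixed before randomization. Report complications that arise afterwards as harms by arm, and do not use them as covariates. Language exposure after randomization would then need its own by-arm summary; how it enters the models is a separate question.

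**Cost.** A few added extract fields (the events above are not among the listed variables, so availability must be checked) and one table. Charted counts are noisy, and intervals will be wide at 21 per arm.

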### Ethics

Our RCT was approved by the Stanford School of Medicine Institutional Review Board (IRB). Informed consent is obtained from the infant’s parent/guardian by research staff in accordance with IRB procedures. The intervention will be overseen by a data safety and monitoring committee comprising two neonatologists and a pediatric neuroradiologist at LCPH.

### Limitations of the study

The present intervention may not significantly change long-term language outcomes or white matter development. It is possible that parents who consent to the study may increase their verbal input to infants, thus swamping treatment effects. However, the amount of speech that neonates typically hear is generally limited and will be vastly increased by the proposed intervention. In addition, individual variations in language exposure following discharge from the NICU may swamp out early gains made by the NICU intervention. If we fail to find long-term effects of the intervention, it may be that naturalistic maternal speech overwhelms the effects of the intervention. Such findings would suggest a need for additional language interventions administered within the first postnatal year (e.g., monthly; every 3 months; quarterly) that could be developed and tested as part of future RCTs.

## Discussion

Despite consistent evidence linking preterm birth to delays in language development, few clinical interventions for promoting healthy language development currently exist. To our knowledge, the present RCT is the first designed to assess the impact of increased exposure to maternal speech on long-term language outcomes and white matter brain development. By examining the potential changes induced by increased exposure to maternal speech on white matter connectivity, this RCT may promote changes in infant brain development that may serve as a marker of effective intervention and a precursor of future language development. Therefore, the significance of this RCT resides in that we may be able to prevent neurodevelopmental delays before they manifest and thus move the child toward favorable developmental trajectories, by intervening early in the hospital nursery. The ultimate significance of the proposed research will be to establish the nature and timing of language interventions for improving language and neural outcomes in preterm infants.

## Trial status

Protocol version number and date: NCT04193579, December 10, 2019

Date when recruitment began: November 25, 2019

Approximate date when recruitment will end: December 31, 2021

## Data Availability

De-identified data analyzed as part of the current study will be made available upon request to the corresponding author.

## Abbreviations

AA: Age adjusted for prematurity
CDI: MacArthur-Bates Communicative Developmental Inventories
C group: Control group
dMRI: Diffusion magnetic resonance imaging
FA: Fractional anisotropy
GA: Gestational age
IRB: Institutional Review Board
LPCH: Lucile Packard Children’s Hospital
MD: Mean diffusivity
NICU: Neonatal intensive care unit
PICN: Packard intermediate care nursery
PMA: Postmenstrual age
RCT: Randomized controlled trial
REDCap: Research Electronic Data Capture
SES: Socioeconomic status
T group: Treatment group
